### Recruitment

The recruitment process was started through the kindergartens’ software platforms, email, presenting a short demo video on the platforms regarding the study, and information leaflets. A website link of the study’s information, recruitment, and registration was provided in the medium used in the kindergartens. In Finland, the registration will be through a webropol link and emails. In Germany, the registration will be through emails. The anonymity of the participants from the research team will be secured during the process.

### Randomization

The cluster randomization will be at the kindergarten level. Kindergartens will be randomly assigned to control or intervention groups by two researchers that are not members of the research team and are stratified by country. One kindergarten serves as one cluster. Simple randomization will be used which will be drawing lots, where each cluster will be assigned a number in a piece of paper. The parents will enrol their children for participation in the study within the time set through the website link provided and email.

No information will be given regarding the allocation. Allocation will be about four weeks before the start of the baseline phase and will be conducted by the two non-member researchers. They will generate the allocation sequence, enroll the participants, and assign them to control or intervention groups. There will be complete concealment of the allocation from the members of the research team and the participants, to exclude the possibility of predicting the next allocation [33].

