**Fig 1 pone.0280686.g001:**
[figure not shown]
Schedule of enrolment, intervention, and assessments.

This study will be a four-arm cluster randomized controlled trial study with three phases and a twelve-month follow-up by country stratification. This study will evaluate the effectiveness of the gamified live feedback intervention on children’s handwashing behaviour, self-efficacy, and motivation in three different phases: the baseline, intervention, and post-intervention phases. In Finland, there will be a twelve-month follow-up after the baseline phase. This study will consist of four groups, the control group, and three different intervention groups. All the groups will have automated monitoring systems installed before the start of the baseline phase and will be available in all phases. The system will be de-installed after the post-intervention phase.

During the baseline phase, all the groups will have no screen activity. During the intervention phase, the control group will have no screen activity. The intervention A group will have a screen display providing handwashing instructions but no reward, and the intervention B and C groups will receive handwashing instructions and rewards from the screen display. During the post-intervention phase, all the groups will have no screen activity except the intervention C group which will receive handwashing instructions but no reward (Fig 2).

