### Study setting

This study will be conducted in kindergartens of different locations around Turku, Finland and Bamberg, Germany. In Germany and in Finland, kindergartens are under the supervision of Early Childhood Education and Care (ECEC) [36]. It is a part of Finnish and German education systems which support the children’s development and focus on learning through play. It is an essential stage on the child’s path of growing and learning. ECEC is a systematic and goal-oriented entity that includes upbringing, education, and care, specifically emphasizing pedagogy aiming to promote and support holistic growth, development, health, and wellbeing (Act on Early Childhood and Care). Groups of children in the kindergartens may be formed in various ways, considering the children’s ages or needs for support. Distribution on staffing and maximum group sizes are considered in forming the groups of children. The kindergarten staff are composed of preschool teachers and assistants who are responsible for the daily activities of the children [36–39].

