### Sample size

The sample size is calculated based on the significant effects found during the pre-study. In the pre-study, 10,000 handwashing events were recorded over a period of 42 days in a treatment group (n = 82 children in two clusters) and a control group (n = 53 children in two clusters). Using Cohen’s power analysis with f^2^ = 0,35 (large effect size) and power level of 0.8 and 2 predictors and a probability level of 0.05 leads to n = 31. However, since randomization is on a cluster level, the n must be increased. With the ICC from the pre-study of 0.062, and estimated cluster size (size of each kindergarten) of 40 children, we calculate the design effect:

D=1+(m−1)*ICC=1+(40−1)*0.062=3.418

Thus, we need to increase the sample size by 3.418 compared to individual randomization, due to cluster randomization leading to 106 participants (n = 31 * 4.418 = 106). With the assumption of a cluster size of 40 children per kindergarten, this leads to three kindergartens that need to participate in the study. Each kindergarten represents one cluster and gets assigned to be the control, the intervention A, B, and C groups. Two intervention groups will be covered by one cluster.

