### Data analyses

Data will be analysed using qualitative and statistical methods. All eligible participants will be included in the analysis. The statistical analyses will be performed with R. The categorical and numerical data will be analysed using one-way analysis of variance (ANOVA). Qualitative analysis will be presented thematically [42].

For the measurement data from the system:

Data pre-processing: Data will be investigated where water and soaping data are combined to single handwashing procedures. Data points that are not valid (outside of kindergarten opening hours) will be removed. The descriptive statistics of the clusters, randomization checks, ICC (intracluster correlation) will be calculated. The data will be analyzed using linear fixed-effect regression model for panel data, and dependent variable soaping time. The four groups will be compared in baseline, intervention, and post-intervention phases.

For the survey and staff interview data:

The comparison among the groups will be implemented using random effects regression, allowing for the clustered nature of the data, and adjusted using the covariates of the adjusted analyses (when a small number of clusters are present) [43]. Simple bias analysis will be used to quantify the uncertainty of the biases such as confounding variables [33]. The qualitative results of the survey and kindergarten staff interview will be analysed and compared thematically. The four groups will be compared after intervention phase.

For the children interview and observation data:

The analyses will be compared among groups based on the complete data only. The comparative analyses approach used to calculate the observation, survey, and staff interview will be used. The self-efficacy measurement scale will be developed and evaluated for its psychometric properties [44,45]. The qualitative result of the observation and interviews will be analysed and compared thematically [42]. Children who will participate the interview at one time point will be considered as missing data, these will be excluded from the analysis. The four groups will be compared in baseline, intervention, and post-intervention phases.

For the sickness day data:

The total sick leave days are compared among the groups one year before and after the start of the baseline phase.

The statisticians of the two universities will validate the statistical results of the data.

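### Allocation is called both simple and stratified by country, lots within each country are not stated, and the one-way ANOVA cannot carry the stratification factor.

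*Protocol article*

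**What the plan says.** The Randomization section of the protocol article describes the people who allocate the kindergartens and the allocation itself in one sentence: they are "not members of the research team and are stratified by country". The same paragraph then states: "Simple randomization will be used which will be drawing lots, where each cluster will be assigned a number in a piece of paper". The Trial design section (text under Fig 1) repeats the stratification, calling the study a "four-arm cluster randomized controlled trial study with three phases and a twelve-month follow-up by country stratification". There are two strata: "This study will be conducted in kindergartens of different locations around Turku, Finland and Bamberg, Germany".

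The Data analyses section opens with a general rule: "The categorical and numerical data will be analysed using one-way analysis of variance (ANOVA". It then gives models by data source:

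- **Sensor data:** a linear fixed-effect panel regression of soaping time. The unit of the fixed effect is not stated.
- **Parent survey and staff interview:** a random-effects regression that allows for clustering and adjusts for covariates that are not listed. The groups are compared after the intervention phase.
- **Child interviews and observations:** the same approach, with comparisons at baseline, intervention and post-intervention.
- **Sick leave:** compared among groups. The Outcome measures section limits this outcome to Finland.

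Country is named in none of these.

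**The concern.** Simple randomisation normally means unrestricted allocation, while stratified randomisation is restricted. The two researchers who run the draw could follow either sentence and produce different designs. Only a draw within each country secures the balance that stratification is meant to give.

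The analysis should then carry the factor used in the allocation. A one-way ANOVA has a single factor, and if that factor is arm there is no room for country. At stake is whether a difference between arms can be told apart from a difference between Finland and Germany. The point matters most for the parent survey and staff interview: answers come from Finnish- or German-speaking respondents, and no baseline value is available to remove a gap in level.

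**Working it through.** **1. The plan's own number of kindergartens.** Inputs from the Sample size section: "f^2^ = 0,35 (large effect size) and power level of 0.8 and 2 predictors and a probability level of 0.05 leads to n = 31", ICC 0.062 and 40 children per kindergarten.

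- Noncentral F power with u = 2, v = n − 3 and λ = 0.35n: n = 31 gives 0.804 and n = 30 gives 0.789, so 31 is reproduced.
- Design effect: 1 + (40 − 1) × 0.062 = 3.418.
- Children: 31 × 3.418 = 105.96, so 106. The multiplier printed in the final bracket, 4.418, would give 136.96 and is a misprint.
- Kindergartens: 106 / 40 = 2.65, so 3.

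One kindergarten covers two intervention groups, so there are three lots for four arms. The text does not say whether three is the total or the number per country.

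**2. If three is the total.** Assume both countries take part, so the split is 2 + 1. There are 3! = 6 allocations of the lots.

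- Each lot is held by one kindergarten, so 0 of 6 allocations place any arm in both countries. Drawing within country does not change this.
- Two arms held by different kindergartens lie in different countries whenever one of them has the lone kindergarten: 4 of 6 allocations (67%).
- For a country gap of d standard deviations, the unadjusted post-phase contrast is shifted by −d in 2 allocations, 0 in 2 and +d in 2. The documents give no d. For assumed gaps of 0.2, 0.5 or 0.8 the shift is the full ±0.2, ±0.5 or ±0.8.
- In the four separated allocations a country term cannot be told apart from arm.

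**3. If each country holds every arm (assumed numbers).** Lots drawn within country put every arm in both countries with probability 1. If country were ignored in the draw:

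| Assumed kindergartens | Allocations | Every arm in both countries |
|---|---|---|
| 3 per country, three lots | 6!/(2!)³ = 90 | 3! × 3! = 36 (40%) |
| 4 per country, four lots | 8!/(2!)⁴ = 2520 | 4! × 4! = 576 (23%) |

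These rows show only what the missing words (lots within each country) would secure. They describe neither the stated number of kindergartens nor the stated stratification.

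**4. Which outcomes are exposed.**

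- *Soaping time.* With a kindergarten- or sink-level fixed effect, a constant country level μ cancels from the change since baseline: (μ + δ₁) − (μ + δ₀) = δ₁ − δ₀, where δ₀ and δ₁ are that country's baseline- and later-phase deviations. Only a difference between countries in this change remains.
- *Child interviews and observations.* These are taken at baseline too, so a country gap in level can be seen before the displays are switched on.
- *Parent survey and staff interview.* They have no baseline, so the result of step 2 applies in full unless country is among the unnamed covariates.
- *Sick leave.* Finland only, so no country difference can enter.

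**The case against.** The strongest reply is that nothing contradictory has been shown. Lots drawn within each country satisfy both sentences, and the word simple may describe only the mechanism inside a stratum. The flowchart of the cluster randomisation (Fig 8) is not shown and may settle the layout. This stands: the text is ambiguous and is not a proven contradiction.

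Second, the random-effects model adjusts for unlisted covariates that may include country, a simple bias analysis for confounding is mentioned, and a list of covariates can be left to an analysis plan. This also stands, so a reader should not infer that every planned analysis omits country. It does not rescue the one-way ANOVA, which is fixed in the text and cannot take a second factor. The article does not say which comparisons the ANOVA governs and which fall to the source-specific models.

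Third, a reader might infer that arm and country will probably be confounded, for example from 77% (100% − 23%) for eight kindergartens, or from 4!/4⁴ = 9.4% as the chance that four independently allocated kindergartens in one country cover all four arms. The arithmetic is right. But both figures assume four kindergartens per country and a draw that ignores country, whereas the plan names three kindergartens and declares stratification. They are illustrations and not the risk in this trial.

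**Conclusion.** The point holds as a defect of specification. The method of allocation is not pinned down, and one named analysis cannot carry the declared stratification factor. Its consequence depends on the number of kindergartens, so the two issues cannot be separated:

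- **Three kindergartens in total, split 2 + 1:** no arm occurs in both countries. A given pair of arms held by different kindergartens is separated by country in 67% of allocations, and an unadjusted contrast without a baseline then carries the full country gap. A country term cannot repair this, so some contrasts can only be descriptive.
- **Every arm in both countries:** lots within country already balance it. Including country then brings mainly precision and standard errors that reflect the design. It does not remove confounding.

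The stronger reading, that the planned comparisons will present Finland–Germany differences as effects of the display, is not supported. For soaping time, a kindergarten- or sink-level fixed effect would remove constant country differences, leaving country-specific changes between phases, for which the documents give no figures. These conclusions assume that both countries contribute kindergartens. The gaps of 0.2 to 0.8 SD are assumed.

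**What to change.** 1. In the Randomization section, replace the simple-randomisation wording by lots drawn without replacement, separately within each country, from a fixed set of arm slips that includes control. State the number of kindergartens per country and per arm.
2. In the Data analyses section, replace the one-way ANOVA by the cluster-adjusted model, with country as the stratification factor wherever the compared arms occur in both countries. For the sensor data, state the unit of the fixed effect and add country by phase. If the unit is the kindergarten or sink, the main effect of country is already absorbed and only the interaction enters.
3. Leave sick leave out of this rule, because it is collected in Finland only.
4. Report as descriptive any contrast whose arms do not share a country. If the three kindergartens are the total, some contrasts will fall here whatever the draw.

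The cost is a few sentences in two sections and one or two model terms. Neither new data nor a larger sample is required. The change does not cure having one kindergarten per arm, where arm is confounded with kindergarten even within a country.

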### Blinding

Due to the intervention’s design and purpose, the research team and the participants will have the possibility to know the assignment. Thereby, this study will use double-blinding in which the children, parents, and kindergarten staff, and the statistician will be unaware of which group will receive the content of the intervention. In the informational letters, the feedback display will not be mentioned, the children and kindergarten staff will only know during the intervention phase. Assistant researchers will also be hired to interact with the participants. They will be given limited information, will be unaware of the study’s design, and which group received the content of the intervention.

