### Outcome measures

The primary outcome is the hand hygiene behaviour of the children. The system will measure the hand hygiene activities which includes the start time of extraction, water volume, water temperature, and end time of extraction; from these data, the following data will be derived: average flow rates, approximation of energy consumption, quality and duration of handwashing, and time stamp of soap used.

The secondary outcomes are self-efficacy, intrinsic motivation, hand hygiene behaviour at home from parents’ survey, hand hygiene behaviour in kindergartens from kindergarten staff, and hand hygiene behaviour in the kindergarten by observation sessions. Self-efficacy and intrinsic motivation will be measured from the children’s one-on-one interview, a three-point Likert scale with open-ended questions. The children will be asked easy and simple questions about their hand hygiene performance, self-regulation on motivation, emotional states, and decisional in performing handwashing. They will respond by pointing their answer from the three smiley faces (sad, neutral, and happy). Colourful smiley faces will be constructed to catch the attention of the children. Each question is followed by open-ended questions to explore their opinions regarding the topic asked and to support their answers. The children interview includes introduction of the interviewer and asking simple questions regarding their day or regular activities for the children to feel comfortable. The parent survey will be an electronic survey composed of five-point Likert and open-ended questions about the observed hand hygiene behaviour of the children at home. The kindergarten staff interview will also include five-point Likert and open-ended questions, evaluating the hand hygiene behaviour of the children in the kindergartens. The assistant researchers will observe the hand hygiene behaviour of the children during the handwashing activity in the kindergartens. Observation sessions will include a checklist consisting of the phases of handwashing, the checklist will follow the hand hygiene guideline of the United Nations Children Fund (UNICEF).

The tertiary outcome is the number of sick leave days of the children and kindergarten staff (applies in Finland) considering the seasonal change.

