### Intervention development

The technology for the gamified digital feedback intervention was developed in Germany and the content was developed by the whole research team. It is a child-centred smart hand hygiene intervention. The installations at each washbasin are IoT-based. Each installation will consist of a touchless faucet powered by a digital power box (a), a soap sensor (b), a feedback display (only for treatment groups) (c), and a gateway (d), which connects to the devices (a-c) via Bluetooth and relays data to a cloud infrastructure (e). Connected Information Systems (f), such as dashboards to monitor hand hygiene, can access the system via this cloud infrastructure [40] (Fig 5).

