### Data collection

This study will start in mid-year of 2022 and will last for a year. The data will be analysed using quantitative and qualitative methods. The child’s age and gender will be collected. The implementation phases and timeline of the data collection are shown in Figs 1 and 2.

The handwashing activity data from the system will be recorded every day during the baseline, intervention, and post-intervention phases. The parent survey data will be given and collected within the last week of the intervention phase. The kindergarten staff interview data will be collected during the last week of the intervention phase and right in the beginning week of the post-intervention phase to evaluate the observed effect of children’s hand hygiene behaviour and reactions towards the removal of the instructions and reward. The children’s observation sessions and interviews will be collected during the last weeks of the baseline, intervention, and post-intervention phases. The number of sick leave days will be collected from the sick leave records provided by the kindergarten staff one year before and after the start of the baseline phase.

The follow-up strategy will include sending updates of the study phases through email to the kindergarten managers and staff. The email includes the details of reminding how and when the participants will be contacted for follow-up. It will also include updates on the contact information of the participants.

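### The double-blind label does not fit the design: once displays run, children, staff and on-site observers can see their own kindergarten's condition, so observation and staff ratings are not blinded

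*Protocol article*

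**What the plan says.** The Blinding section opens by conceding that "the research team and the participants will have the possibility to know the assignment". Its next sentence draws the opposite conclusion: "Thereby, this study will use double-blinding in which the children, parents, and kindergarten staff, and the statistician will be unaware of which group" gets the content. It then explains that the information letters leave out the display, so that "the children and kindergarten staff will only know during the intervention phase". Finally it says that hired assistant researchers will have limited information, will not know the design, and will not know "which group received the content of the intervention".

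Other sections describe what can be seen on site. Intervention development lists the equipment at each washbasin, including "a feedback display (only for treatment groups". Implementation places the screen beside the sink and gives the control group none at any time. Under Outcome measures, "The assistant researchers will observe the hand hygiene behaviour of the children during the handwashing activity in the kindergartens", using a checklist of handwashing steps. Data collection schedules these sessions in the last weeks of the baseline, intervention and post-intervention phases. It schedules the staff interview in the last week of the intervention phase and the first week after it, "to evaluate the observed effect of children’s hand hygiene behaviour and reactions towards the removal of the instructions and reward".

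**The concern.** Blinding is a stated property of the design, and readers use it to decide how far to trust outcomes that rest on human judgement. Leaving the display out of the information letters conceals it only until it is switched on. Briefing the observers sparsely does not stop them seeing a screen beside the sink where they are scoring.

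The Discussion presents the monitoring system, survey, interview and observation together as support for effectiveness. If the observation and staff ratings are read as blinded, they appear to be independent confirmation of the sensor result. If the raters know the condition, they are weaker evidence.

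**Working it through.** No arithmetic applies, because no figure in the document bears on this point. The check compares who is said to be blind with what each party can see.

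**What is visible at the sink, by arm and phase** (Trial design and Implementation):

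| Phase | Control | A | B | C |
|---|---|---|---|---|
| Baseline | no screen activity | no screen activity | no screen activity | no screen activity |
| Intervention | no screen | instructions | instructions and reward | instructions and reward |
| Post-intervention | no screen | no screen activity | no screen activity | instructions |

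In the intervention phase an observer at the sink can tell control, A, and B or C apart; B and C look the same. In the post-intervention phase C can be told from the rest. At baseline screen activity reveals nothing, so concealment at that stage is feasible.

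**Each party in turn:**

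- *Children and staff.* The Blinding section itself says they will know during the intervention phase. The staff interview asks about the removal of instructions and reward, which presupposes knowing what was delivered.
- *Assistant researchers.* They watch handwashing in the kindergartens in the last week of each phase. That they see the screen is an inference from where and when they observe, but it is hard to avoid: in B and C the animation follows a correct wash, which is the event being scored.
- *Parents.* They report on behaviour at home and are not at the sink. Nothing shows that they must know the arm, although a child may tell them.
- *Statistician.* Nothing in the document contradicts this blinding.

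**Outcomes affected.** Five secondary outcomes are listed: self-efficacy, intrinsic motivation, parent-reported behaviour at home, staff-reported behaviour, and observed behaviour. Two of the five, staff report and observation, are ratings of handwashing by people who can see the condition. The primary outcome comes from the automated system. Sick leave days, the tertiary outcome, come from kindergarten records.

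**Safeguards.** Limitations discusses the Hawthorne effect, which concerns children reacting to being watched. Data analyses plans a simple bias analysis for survey and staff data and gives confounding variables as its example. Neither addresses raters who know the arm.

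**The case against.** The strongest reply is that the protocol discloses much of this already. It says that the assignment can become known and that children and staff will learn of the display, and it openly asks staff about its removal. For staff, then, the fault is mainly a label that contradicts the text around it. This stands; the undisclosed part is the claim about the assistant researchers.

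Partial masking also has value. Staff and children in one kindergarten need not know what other kindergartens receive, and observers who see a screen may still be unaware of the other arms and the hypotheses. That weakens an expectation effect. It does not remove it, since knowing that a feedback display is running is enough to create an expectation.

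Four stronger readings are tempting, but the documents do not support them:

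- *The plan denies that bias exists.* No section says so. It asserts blinding, which implies protection, but it also concedes awareness and lists a source of bias in observation.
- *Only the statistician can be blinded.* Parents, and knowledge of the other arms, can plausibly stay masked.
- *Only the sensor outcome is free of assessor judgement.* Sick leave records involve no rating of handwashing, and the children's interview answers are self-report.
- *The bias uniformly favours the display arms.* That is plausible while displays run, given H1. After removal, however, H3b expects B to return to baseline and H3c expects A to fall below it, so expectation need not favour those arms.

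It can also be said that the sensor measure is already primary and the rated outcomes already secondary. That is true, and it limits the consequence to how the secondary outcomes are described and interpreted.

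**Conclusion.** The point holds in a limited form. The double-blind label conflicts with the Blinding section's own text, and the claimed unawareness of the assistant researchers cannot be kept once they score beside a running display. Children, staff and on-site observers are not blind to their own kindergarten's condition from switch-on.

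The consequence falls on the observation checklist and the staff Likert ratings. For observation it arises in the intervention phase, when all three treatment arms have running displays, and in the post-intervention phase for C. For staff it covers both interview times. The bias is of unknown size, and its direction after removal is not established. A reader might infer that the trial's main result is compromised; it is not on this ground, because the primary outcome is recorded by sensors and rater judgement does not reach it directly.

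The conclusion rests on one assumption beyond the text: that observers placed to watch handwashing can see a screen mounted beside the sink.

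**What to change.** In the Blinding section, replace the double-blind statement with one that says:

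- allocation is not disclosed until the displays are switched on;
- from then on, children, staff and on-site observers are aware of their own kindergarten's display, though they are not informed of the other arms or the hypotheses;
- parents are not informed of the allocation;
- the statistician is blinded.

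Delete the claim that assistant researchers do not know which group received the content. State that the observation and staff ratings will be reported as unblinded, supportive outcomes, and that conclusions on effectiveness rest on the sensor outcome.

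The design, primary outcome and primary analysis do not change. The cost is a text edit and a less favourable blinding statement.
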